#### Exploratory endpoints

Levels of peritoneal inflammatory response in peritoneal fluid expressed by: Eotaxin, Eotaxin-3, GM-CSF, IFN-γ, IL-1α, IL-1β, IL-2, IL-4, IL-5, IL-6, IL-7, IL-8, IL-8 (HA), IL-10, IL-12, IL-13, IL-15, IL-16, IL-17A, IP-10, MCP-1, MCP-4, MDC, MIP-1α, MIP-1β, TARC, TNF, LT-α, VEGF-A, as well as IL-1RA and CRP measured on the first three postoperative days.Patient-reported health-related quality of recovery-15 (QoR-15) [29].30 days mortality rate.Heart rate variability.Gene transcript (mRNA) analysis.Comparison of the systemic and peritoneal inflammatory response in relation to the risk of cancer recurrence 3 years postoperatively.

### Participant timeline, data collection and follow-up

The preoperative assessment will consist of information concerning baseline data (age, gender, body-mass index (BMI), ASA-score, Charlson Comorbidity Index (CCI), WHO performance status, date of diagnosis, type of planned operation, date of randomization and operation (Figs. 1 and 2). Patients will be preoperatively asked to fill out the QoR-15 questionnaire at baseline and from the first until the third postoperative day [29]. A full recovery status (QoR-15) will be collected 14 days postoperatively.

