### Recruitment, randomization and blinding

A total of 50 patients (25 in each arm) will be recruited for randomization in the period 1st August 2021–1st September 2022 at the Surgical Department, Hospital Sønderjylland, University Hospital of Southern Denmark. The screening of potential candidates eligible for randomization will occur at a multidisciplinary colorectal cancer conference held twice weekly at the study site. Patients will be randomized according to transparent reporting of trials (CONSORT) on a 1:1 basis to either robot-assisted or laparoscopic surgery (Fig. 3). A computer-generated randomization sequence program (REDCap®) managed by the project owner will allocate patients to robot-assisted or laparoscopic colectomies. The program is provided with personal identification numbers that will be utilized, whereby data can be pseudo-anonymized. Subsequently, information material about the trial will be provided, including a health quality questionnaire. The study participants and data assessor will be blinded. The randomization will require the following information:Age and sexConfirmation that inclusion and exclusion criteria are metConfirmation of informed consentPlanned date of operationType of operation

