### Statistics

Descriptive statistics will be utilized to check for exchangeability between the two groups according to baseline variables. Categorical variables will be analyzed with a Chi-square or Fischer’s exact test depending on Cochran’s rule. Continuous and discrete variables will be analyzed with an unpaired t-test or Wilcoxon rank-sum test depending on the distribution of the variables. The primary, secondary and exploratory endpoints will also be compared using descriptive statistics. For continuous and discrete variables, repeated measurement ANOVA or Kruskal–Wallis rank-sum tests will be used to compare these variables across timepoints stratified according to the operation method. The normality and heterogeneity of variance assumptions for the t-test and the ANOVA will be graphically assessed using quantile–quantile plots. A mixed-effect model will be utilized to analyze the degree of systemic and peritoneal inflammatory response because of repeated measurements. Logistic regression will be utilized to analyze perioperative complications, 30-day mortality, surgical and medical complications. Odds ratios with 95% confidence intervals will be reported. A poisson or linear regression will be used for time from treatment start until end, and the Quality of Recovery questionnaire (QoR-15 score). Quantile–quantile plots will be used to check if the deviance and the Pearson residuals are normally distributed, and a scatterplot of the deviance and Pearson residuals will check the closeness of the model to our data. If the residuals for the mixed-effect model are not normally distributed, a log transformation of the outcome may be necessary. If the residuals are still not normal distributed, a mixed-effect gamma model will be performed. If these residuals are not normally distributed, logistic regression with another type of link function will be utilized. If deviance residuals are not normally distributed and are not close to zero for the poisson regression, a negative binomial regression or linear regression with bootstrapped confidence intervals will be utilized. If adjustments in the mixed-effect model are necessary, a univariate analysis with only the exposure variable will be included as a sensitivity analysis. If the negative binomial regression is utilized, a poisson regression will be added as a supplementary analysis. No subgroups analysis will be a part of this project. All regression analyses will follow the one-in-ten rule to avoid overfitting. No interim analyses will be performed as no similar prospective randomized clinical trial has previously been performed, so completion of this study is of great importance.

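### The regression stated for QoR-15 gives the preoperative score no role, so the exploratory arm comparison is probably less precise than it could be

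*Protocol article*

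**What the plan says.** All references are to the protocol article.

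- **Collection** (Participant timeline, data collection and follow-up): "Patients will be preoperatively asked to fill out the QoR-15 questionnaire at baseline and from the first until the third postoperative day". The same section adds: "A full recovery status (QoR-15) will be collected 14 days postoperatively". That makes one score before surgery and four after it.
- **Status** (Exploratory endpoints): QoR-15 is listed there, not among the primary or secondary endpoints.
- **Model** (Statistics): "A poisson or linear regression will be used for time from treatment start until end, and the Quality of Recovery questionnaire (QoR-15 score". No covariate is named, and no change from baseline is defined.
- **Adjustment** (Statistics): "If adjustments in the mixed-effect model are necessary, a univariate analysis with only the exposure variable will be included as a sensitivity analysis". The mixed-effect model is the one assigned to the systemic and peritoneal inflammatory response.
- **Limit on model terms** (Statistics): "All regression analyses will follow the one-in-ten rule to avoid overfitting".
- **Size** (Recruitment, randomization and blinding): "A total of 50 patients (25 in each arm) will be recruited for randomization".

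**The concern.** The trial plans to measure QoR-15 before surgery on the same instrument that it later compares between arms. The model sentence for that comparison leaves the preoperative score out. The only stated use of baseline variables is a descriptive check of whether the groups are comparable. Such a check can show an imbalance but does not take it out of the arm difference.

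Two things are at stake at 25 patients per arm. If the preoperative score predicts the later one, spread between patients that could be removed stays in the error term. And in any one trial, a chance preoperative difference between the arms carries into the estimated recovery difference. QoR-15 is the only patient-reported recovery questionnaire among the listed endpoints, so its comparison should be made as sharp as the planned data allow.

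**Working it through.** **Plan's own figure.** The article gives no power, precision or correlation for QoR-15. Its only power calculation is for CRP, which does not bear on this point and is not used here.

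**Inputs.** N = 50, 25 per arm (Recruitment, randomization and blinding). The correlation r between the preoperative and a postoperative QoR-15 score is not in the article. It is an assumption, shown over 0 to 0.7.

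**Step 1: variance with and without the baseline score.** Take the linear option and one postoperative day, with σ the SD of the score. The unadjusted arm difference has variance σ² × (1/25 + 1/25) = 0.08σ². Adding the baseline score multiplies this by

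(1 − r²) × (1 + 1/(N − 4)) = (1 − r²) × (1 + 1/46) = (1 − r²) × 1.0217.

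The second factor is the cost of estimating one more coefficient in a small trial. The confidence interval scales with the square root of the ratio, and the equivalent sample size is 50 divided by the ratio.

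| assumed r | variance ratio | CI width ratio | equivalent N |
|---|---|---|---|
| 0 | 1.022 | 1.011 | 49 |
| 0.1 | 1.012 | 1.006 | 49 |
| 0.2 | 0.981 | 0.990 | 51 |
| 0.3 | 0.930 | 0.964 | 54 |
| 0.5 | 0.766 | 0.875 | 65 |
| 0.7 | 0.521 | 0.722 | 96 |

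Simulation of 20,000 trials of 25 per arm gave variance ratios of 1.023, 0.932, 0.767 and 0.524 at r = 0, 0.3, 0.5 and 0.7, in agreement with the formula.

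**Step 2: break-even.** The ratio equals 1 when 1 − r² = 46/47, so r² = 1/47 = 0.0213 and r is about 0.15. Below that, adjustment costs a little, at most about 2% of variance. Above it, adjustment gains.

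**Step 3: chance imbalance.** The difference in mean preoperative score between arms has SD √(2/25) = 0.283 baseline SDs, so its 95% range is ±1.96 × 0.283 = ±0.55. Without adjustment, r times the realised imbalance passes into the arm difference. The 95% range of that carry-over, in SDs of the postoperative score, is:

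- r = 0.3: ±0.17
- r = 0.5: ±0.28
- r = 0.7: ±0.39

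This is the same loss as in Step 1, seen within a single trial. It is not an additional one.

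**Step 4: is there room for the term?** Read as one term per ten patients, the one-in-ten rule allows 50/10 = 5 terms. Arm plus baseline score uses two. The score is taken before surgery and participants are to be blinded, so it can serve as a covariate.

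**The case against.** The strongest objection is that the case rests on silence. The model sentence names a family of regressions and no covariates of any kind; it does not say the model is unadjusted. The article condenses a fuller protocol, and a covariate list for an exploratory endpoint is often left to an analysis plan. The one-in-ten rule covers all regressions and suggests that models with covariates are contemplated. This stands in part: a reader might infer that the plan rules out the baseline score, and the text does not support that. What remains is that the Statistics section is specific elsewhere. It fixes residual checks, fallback models and a sensitivity analysis for an adjusted mixed model, and it chooses a model for QoR-15 without giving the baseline score a place. A regression on arm alone is the natural reading.

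A second objection is that the preoperative score may be used in another stated analysis: "repeated measurement ANOVA or Kruskal–Wallis rank-sum tests will be used to compare these variables across timepoints stratified according to the operation method". The article does not say whether the preoperative score counts as one of these timepoints, so one cannot conclude that it is never used. But a comparison of timepoints within each operation method does not yield a baseline-adjusted difference between arms.

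A third objection is that the gain depends on a correlation the article does not give. That is correct. The gain is not free in every case, which is why the table includes low values and the break-even point.

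**Conclusion.** The point holds as a low-priority improvement. As stated, the QoR-15 regression gives the preoperative score no role, and the arm comparison is probably less precise than it could be. At N = 50 the variance would fall by about 7%, 23% or 48% at r = 0.3, 0.5 or 0.7, against a worst-case cost of about 2%.

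These figures assume the linear option, a single postoperative day, 25 analysed patients per arm with complete scores, and the same linear relation to baseline in both arms. They do not carry over exactly to the Poisson option.

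A reader might infer that the unadjusted comparison is biased. It is not: under randomisation, chance imbalance averages out over repeated trials, and the matter is one of precision and of conditional bias in the trial at hand. Nor does the point reach the primary endpoint, the sample size or the alpha level. It also assumes that patients complete the preoperative form; the article says only that they are asked to.

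**What to change.** Add one sentence to the Statistics section, or to the analysis plan before the data are seen: the preoperative QoR-15 score enters the regression of the postoperative scores as a covariate, and the baseline-adjusted arm differences at days 1–3 and day 14 are the main QoR-15 result. An unadjusted difference can be shown beside it. If the analysis plan already says this, a cross-reference is enough.

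The cost is one coefficient and one degree of freedom. No new data are needed, and the one-in-ten rule is respected. Fixing it in advance also removes a later choice between adjusted and unadjusted results.

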**Fig. 1 Fig1:**
[figure not shown]
Schedule of Enrolment, Interventions, and Assessments (SPIRIT figure)

**Fig. 2 Fig2:**
[figure not shown]
Participant timeline

Short-term results and long term follow up of the study (peritoneal inflammatory response in comparison with systemic inflammatory stress response and the 3-year cancer recurrence) will be published separately. All sample data will be entered into an electronic database program (REDCap ®) hosted by the Open Patient data Explorative Network (OPEN), available only to project owners, ensuring that anonymity is maintained and data security is respected. Consent statements from participants in the study will be stored in accordance with GDPR regulations [30]. Ethical principles for medical research will follow the Helsinki declaration [31]. Blood samples and peritoneal fluid will be stored at a secure local study site. Once all patients are included in the study, the samples will be transferred to the Department of Neurobiology, the University of Southern Denmark, for laboratory analysis. Gene transcription analysis (mRNA) will be completed at the Zealand University Hospital, Køge, Denmark.

### Sample size

The Monte Carlo method calculated the power of the mixed effect model used for the log-normal distributed outcome of C-reactive protein (CRP) levels. The sample size calculation was based on the primary outcome (the systemic inflammatory postoperative response expressed by pro-inflammatory and anti-inflammatory cytokines). It was assumed that the CRP level in the group of patients undergoing laparoscopic surgery for colorectal cancer would be 19% higher than patients with robot-assisted surgery, with an interpersonal variation of 0.63 and an intrapersonal variation of 0.34 for the logarithmic transformed CRP. The mixed-effect model was adjusted for type of operation and time. The assumption of CRP among elective malignant colonic resections was based on postoperative measurements on days 1–3 from an observational data set of 298 patients undergoing surgery for colorectal cancer using robot-assisted or laparoscopic methods from 2017 to 2019 at our surgical department, Hospital Sønderjylland, University Hospital of Southern Denmark  [17]. To obtain a power of 86% and an alpha level of 0.05 for a two-sided p-value, we aimed to include a minimum of 42 patients.

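### The stated 86% power for a 19% CRP difference with 42 patients does not follow from the stated inputs, which give about 13% (15% with the planned 50)

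*Protocol article*

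**What the plan says.** All the inputs are in the protocol article, under Sample size. Power was obtained by Monte Carlo simulation of a mixed-effect model for log-normal CRP, adjusted for type of operation and time. The effect is that CRP in the laparoscopic group "would be 19% higher than patients with robot-assisted surgery". The variability is an "interpersonal variation of 0.63 and an intrapersonal variation of 0.34 for the logarithmic transformed CRP". These assumptions come from measurements on postoperative days 1 to 3 in a departmental data set of 298 patients. The conclusion is a minimum of 42 patients: "To obtain a power of 86% and an alpha level of 0.05 for a two-sided p-value".

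Under Recruitment, randomization and blinding, allocation is 1:1 and the target is larger: "A total of 50 patients (25 in each arm) will be recruited for randomization".

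The text does not say whether 0.63 and 0.34 are standard deviations or variances, or which log base was used.

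**The concern.** Each patient has only one operation, so the arms are compared between patients. Averaging three days shrinks the within-patient part of the variance and leaves the between-patient part untouched. With a between-patient spread of 0.63 on the log scale, a 19% difference in level is small, and about 21 patients per arm would not be expected to detect it reliably.

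The Sample size section is the article's only justification for the size of what it calls a superiority trial. If the power is really near 15%, the trial would miss the assumed effect about 85% of the time even if that effect is real. A reader who relies on the published 86% would then give a non-significant result far more weight than it can bear.

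**Working it through.** **Inputs** (Sample size; Recruitment, randomization and blinding): CRP ratio 1.19; between-patient 0.63 and within-patient 0.34 on log CRP; 3 measurements per patient; two-sided 5%; 21 per arm (42 in total) or 25 per arm (50 in total).

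**Attempt to reproduce 86%, SD reading, natural logs**

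- Effect: ln(1.19) = 0.174.
- Variance of a patient's three-day mean: 0.63² + 0.34²/3 = 0.3969 + 0.0385 = 0.4354, so SD = 0.660.
- Standard error of the arm contrast, √(2 × 0.4354/n): 0.204 with 21 per arm and 0.187 with 25 per arm.
- Effect divided by standard error: 0.174/0.204 = 0.85 and 0.174/0.187 = 0.93.
- Power (noncentral t): **13.3%** with 42 patients and **15.0%** with 50. A simulation of 40,000 trials, tested on patient means (equivalent to the mixed model in balanced data), gave 13.3% and 15.0%.

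The stated 86% is not reproduced.

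**Other readings of the same inputs**

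| Reading | 42 patients | 50 patients |
|---|---|---|
| SDs, natural log | 13% | 15% |
| Variances, natural log (0.63 + 0.34/3 = 0.743) | 10% | 11% |
| SDs, log base 2 | 23% | 26% |
| SDs, log base 10 | 7% | 7% |

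Further variants at 21 per arm, SD reading: one-sided test 21%; the two labels swapped 20%; 0.63 as the total SD 17%. Reading 42 as the number per arm gives 22%. Baseline adjustment, which the sample size text does not mention, gives 30–35%. A different contrast, 19% per day as a slope, gives 65%.

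**Can more samples per patient help?** With within-patient variation set to zero, the patient-mean SD is 0.63 and power with 42 patients is still only 14%.

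**What would 86% require?** With 21 per arm and an effect of 0.174, the patient-mean SD would have to be about 0.18, a variance of about 0.033. The within-patient part alone contributes 0.0385. Keeping the SD at 0.660 instead, about 267 per arm would be needed.

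**Two routes that come near 86%**

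1. Between-patient term left out: patient-mean SD = 0.34/√3 = 0.196. A t-test on patient means with 21 per arm gives 80% with 0.174 as the effect and 86% with 0.19 used directly as the log difference.
2. 19% applied to the mean of log CRP, with both variance components kept: effect = 0.19 × ln(geometric mean CRP). The document does not give that mean, so the following are assumed values. On the SD reading with 21 per arm, power is 78%, 84%, 95% and 98% at 20, 26, 50 and 80 mg/L, and passes 86% at about 28 mg/L. On the variance reading it is 55%, 62%, 78% and 86% at the same values, and passes 86% at about 79 mg/L. The CRP ratio then powered for is about 1.9 or 2.3, not 1.19.

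**What 50 patients can show if the inputs stand** (t-based): 86% power is reached at a ratio of about 1.78 (SD reading) or 2.13 (variance reading). On the SD reading the expected 95% CI is the estimated ratio times or divided by exp(2.01 × 0.187) = 1.46, for example 0.82 to 1.73 around 1.19.

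**The case against.** The strongest objection is that the simulation may have been sound and only its description wrong. If 19% was applied to the mean of log CRP, 86% is attainable with the random intercept in place. This stands as a possibility. It does not rescue the text, which says that the CRP level is 19% higher; on this route the effect statement is what needs correcting.

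For the same reason, a reader might infer that the simulation must have omitted the patient random intercept, since one version of that omission gives 86%. The document does not support this as the explanation. At least two routes lead to the figure, and neither the code nor the source data are shown.

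A reader might also infer that the investigators will take a non-significant result as showing no difference. Nothing in the article says so. The point is only that the published power figure invites that reading.

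Finally, the ambiguity of the word variation means that no single replacement figure can be fixed now. This is right, and it limits the wording of the correction. It does not affect the finding, because no reading that keeps both stated components and a 19% higher CRP level between arms comes near 86%.

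**Conclusion.** The stated power is wrong as written. On the protocol's own inputs it is about 13% with 42 patients and 15% with 50 (SD reading), or about 10% and 11% (variance reading), against 86% claimed. The most favourable log base tried, base 2, gives 23% and 26%.

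This rests on three measurements per patient, a random-intercept structure with the two stated components, 1:1 allocation, complete data, and 19% meaning a ratio of CRP levels. The source of the error cannot be determined from the document. This is a contradiction between a stated figure and its stated inputs, so it does not depend on anything a separate analysis plan might add.

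**What to change.** 1. Re-run the Monte Carlo calculation with a patient random intercept and arm as a between-patient factor.
2. State whether 0.63 and 0.34 are SDs or variances, which log base applies, and whether 19% is a ratio of CRP levels.
3. Once that is settled, replace the 86% statement with the power obtained for 50 patients and the ratio detectable at 86% power. If the inputs stand as written, these are about 15% and 1.78 (SD reading) or about 11% and 2.13 (variance reading).
4. State that a non-significant result will not be read as absence of a difference, and report the geometric mean ratio of CRP with its 95% CI.

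The cost is one re-run simulation, revised wording in the sample size section, and a less favourable stated power. No extra patients are needed to make this correction. Equally, it leaves the trial's actual power where it is: it puts right the claim and its interpretation, not the design.

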### Recruitment, randomization and blinding

A total of 50 patients (25 in each arm) will be recruited for randomization in the period 1st August 2021–1st September 2022 at the Surgical Department, Hospital Sønderjylland, University Hospital of Southern Denmark. The screening of potential candidates eligible for randomization will occur at a multidisciplinary colorectal cancer conference held twice weekly at the study site. Patients will be randomized according to transparent reporting of trials (CONSORT) on a 1:1 basis to either robot-assisted or laparoscopic surgery (Fig. 3). A computer-generated randomization sequence program (REDCap®) managed by the project owner will allocate patients to robot-assisted or laparoscopic colectomies. The program is provided with personal identification numbers that will be utilized, whereby data can be pseudo-anonymized. Subsequently, information material about the trial will be provided, including a health quality questionnaire. The study participants and data assessor will be blinded. The randomization will require the following information:Age and sexConfirmation that inclusion and exclusion criteria are metConfirmation of informed consentPlanned date of operationType of operation

